## Abstract

**Background:**

First metatarsophalangeal (MTP) joint osteoarthritis (OA) is a painful and debilitating condition affecting nearly one in 10 people aged over 50 years. Non-drug, non-surgical treatments are recommended by OA clinical guidelines, yet there have only ever been two randomised controlled trials (RCTs) evaluating such strategies in people with first MTP joint OA. Foot orthoses are a common non-drug, non-surgical strategy used by allied health professionals for people with first MTP joint OA, however, it is unknown whether these devices are effective in improving the symptoms associated with the condition. This clinical trial aimed to determine whether contoured foot orthoses lead to greater reductions in first MTP joint pain on walking compared to sham flat insoles in people with first MTP joint OA.

**Methods:**

The FORT trial (Foot ORthoses for big Toe joint osteoarthritis) is a two-arm participant- and assessor-blinded, multi-site RCT conducted in Melbourne, Sydney, Brisbane and the Gold Coast, Australia. We are recruiting 88 community-dwelling people with symptomatic radiographic first MTP joint OA. Following baseline assessment, participants are randomized to receive either: i) contoured foot orthoses; or ii) sham flat insoles following baseline assessment. Participants have two visits with a study podiatrist where they are provided with their allocated insoles, to be worn daily for 12 weeks at all times when wearing shoes. The primary outcome is self-reported first MTP joint pain on walking (numerical rating scale), assessed at baseline and 12 weeks. Secondary outcomes include additional measures of first MTP joint and foot pain, physical function, quality of life, participant-perceived global ratings of change (pain and function), and level of physical activity.

**Discussion:**

This study will provide novel evidence about whether contoured foot orthoses improve pain and other symptoms compared to sham insoles in people with first MTP joint OA. Outcomes will help to inform clinical guidelines and practice about the use of foot orthoses for managing symptoms in this under-researched group of people with OA.

**Trial registration:**

Prospectively registered with the Australian New Zealand Clinical Trials Registry (reference: ACTRN12619000926134) on 3/07/2019.

## Background

Osteoarthritis (OA) of the foot affects 16.7% of people aged 50 years and older, making it as prevalent as knee OA [1], and the most commonly affected foot site is the first metatarsophalangeal (MTP) joint [2]. First MTP joint OA is highly debilitating with most (72%) of those affected reporting the symptoms as disabling [2]. The condition causes dorsal osteophytes and joint space narrowing which impair range of motion, and in turn, lead to substantial problems performing functional weight bearing activities and impaired quality of life [3]. Non-drug, non-surgical strategies are recommended as first line treatments in international OA clinical guidelines [4–7], however there have only ever been two randomised controlled trials (RCTs) of these treatments for first MTP joint OA [8, 9], and one randomized clinical feasibility study [10]. Accordingly, foot OA has been highlighted as an under-researched problem [11] and identified as a research priority by OA experts and all leading international OA clinical bodies [4, 12, 13].

People with first MTP joint OA walk with altered foot biomechanics, displaying reduced joint range of motion and greater maximum force and peak plantar pressures under the hallux [14–16], which may contribute to symptom severity. Foot orthoses with a cut-out under the first MTP joint have been shown to reduce hallux plantar pressures in people with first MTP joint OA [17] and improve the first metatarsal angle and MTP joint range of motion in people with limited first MTP joint movement [18]. Furthermore, a case series has shown they may have beneficial effects on pain in a small group of people with mechanically induced first MTP joint pain [19], suggesting these biomechanical devices may improve clinical symptoms associated with first MTP joint OA. We have also shown that foot orthoses are commonly used in clinical practice. Results of our international survey of podiatrists and physiotherapists who currently treat people with first MTP joint OA showed that foot orthoses were one of the most commonly employed treatment strategies to manage the condition [20].

To date, only one RCT has investigated whether foot orthoses are effective in treating the symptoms associated with first MTP joint OA. Menz and colleagues reported that foot orthoses and rocker-sole footwear both improved pain above the minimal clinically important difference, with no statistically significant difference between the two interventions [9]. However, the use of an active comparator as the control condition in this study means it is unclear whether the clinical improvements seen in both treatment groups were due to true effects of the interventions, placebo effects, or to other factors such as natural history or regression to the mean. The need for such research has also been highlighted by OA stakeholders and patients, who have rated non-surgical treatment and biomechanical strategies within their top 10 OA research priorities [21].

This study protocol describes a clinical trial that compares the effects of contoured foot orthoses and sham flat insoles in people with symptomatic radiographic first MTP joint OA. The primary aim is to determine whether daily wear of contoured foot orthoses results in significantly greater reductions in first MTP joint pain with walking over 12 weeks compared to sham flat insoles, in people with first MTP joint OA. The secondary aim is to determine if contoured foot orthoses improve additional measures of pain, function, quality of life and physical activity when compared to sham flat insoles, at 12 weeks.

## Methods

### Study design

The FORT (Foot ORthoses for big Toe joint osteoarthritis) RCT is a participant- and assessor-blinded trial, conducted at sites in Melbourne, Sydney, Brisbane and the Gold Coast in Australia. It was prospectively registered with the Australian and New Zealand Clinical Trials Registry (ACTRN12619000926134) and ethical approval has been obtained from the University of Melbourne Human Research Ethics Committee (HREC No. 1954551). This protocol paper is described using the 2013 SPIRIT guidelines on standard protocol items for clinical trials [22].

### Participants

Community-dwelling participants with symptomatic radiographic first MTP joint OA are recruited via advertisements in print and social media, and using our clinician network and volunteer database. As there are no accepted clinical diagnostic criteria for first MTP joint OA, we are using National Institute for Health and Care Excellence OA criteria [4] combined with radiographic features of first MTP joint OA [23]. Participants are eligible if the following inclusion criteria are met:
i)aged > 45 years,ii)report first MTP joint pain on most days of the last month and for at least 12 weeks,iii)report a minimum pain score of 3 on an 11-point numerical rating scale during walking over the previous week,iv)evidence of radiographic OA (a score of 2 or more for osteophytes or joint space narrowing according to a radiographic atlas [23]), andv)report either no morning joint-related stiffness in the first MTP joint, or morning stiffness that lasts no longer than 30 min.

Participants are excluded if they:
i)have had previous foot surgery on the affected side or are planning surgery in the next 12 weeks,ii)currently use foot orthoses or ankle braces,iii)currently primarily use high heels, sandals or other shoes that would restrict ability to wear orthoses,iv)have had any foot injections on the affected side in the past 6 months or are planning injections in the next 12 weeks,v)report any other current muscular, joint or neurological condition affecting lower limb function,vi)have pain in another location that is greater than the pain in the study first MTP joint,vii)report any systemic or inflammatory joint disease (eg rheumatoid arthritis),viii) have grade 3 or 4 hallux valgus on the affected side [24],ix)currently use or are planning to use a gait aid in the next 12 weeks,x)are unable to understand written/spoken English,xi)are unable to commit to study requirements (eg wearing insoles, attending appointments, completing outcomes).

### Procedure

Figure 1 outlines the flow of participants through the trial and Table 1 describes the schedule of enrolment, interventions and the outcome measures for this study, according to SPIRIT recommendations [22]. Potential volunteers receive study information that describes the aims, potential risks and protocols involved. Volunteers are screened by an online form, then over the phone by the Trial Coordinator. All participants then provide informed consent. Potentially eligible participants undergo standardised dorsoplantar and lateral weightbearing x-rays at radiology clinics in Melbourne, Sydney, Brisbane or the Gold Coast. Participants who have had a previous (past 12 months) weightbearing dorsoplantar and lateral x-ray, and can provide the images, do not have new x-rays due to ethical concerns of exposure to unnecessary radiation. X-rays are assessed for eligibility by an experienced researcher (KP). For participants with bilaterally eligible feet, the most symptomatic foot is used as the study foot for outcome measurements.

**Fig. 1 Fig1:**
[figure not shown]
Flow diagram of s tudy phases

**Table 1 Tab1:**
[figure not shown]
Schedule of enrolment, interventions and assessments

*W* week, *MTP* metatarsophalangeal, *AQoL-6D* Assessment of Quality of Life instrument (version 6D), *PASE* physical activity scale for the elderly

Paper-based or electronic baseline assessments are completed by participants at home. Once the baseline questionnaire has been completed and returned to the researchers, participants are enrolled in the study and randomly allocated to one of the two study groups. After enrolment, a researcher contacts the participant to arrange their two appointments with their podiatrist where they are provided with a pair of their allocated insoles. The participant is advised to choose a participating podiatry clinic that is most convenient for them. Self-reported outcomes are completed at the participant’s home either electronically or on paper at 12-weeks.

### Randomisation, blinding and allocation concealment

Participants are randomised to either the contoured foot orthoses group or the sham flat insoles group using a randomisation schedule prepared by the study biostatistician. Randomisation occurs on a 1:1 allocation with permuted block sizes of 6 to 12, stratified by podiatrist/clinic. The schedule is uploaded and stored on a password-protected website (REDCap) where access is limited to a researcher not involved with participant recruitment or outcome measure administration to ensure concealment. Group allocation is revealed by a different researcher not involved in either participant recruitment or data collection after baseline outcomes have been completed.

Limited disclosure is used to blind participants to group allocation. Participants are told that this clinical trial is comparing two types of insoles but they are not informed about the characteristics of the insoles provided to either group, consistent with our previous insole and footwear OA trials [25, 26]. Participants are also not informed about the specific aims or hypotheses of the study until after the study is completed. At this time, participants will be given a summary outlining the study purpose and main findings. Primary and secondary outcomes are participant-reported, thus this study is also assessor-blinded (because participants are blinded). Study researchers entering participant-reported data will be blinded, as will the study biostatistician performing the statistical analyses. The podiatrists administering the insoles will not be blinded, which is a recognised difficulty when conducting trials using a physical intervention [27]. Stratification by podiatrists/clinics will ensure each podiatrist will treat a similar proportion of participants in both groups to ensure that the effects of podiatrist personality on the therapeutic alliance are consistent across groups.

### Insole interventions

Table 2 describes the contoured foot orthoses and the sham flat insoles. Participants in both groups have two visits with a study podiatrist, one in week 1 and one in week 3. The initial consultation is 30 min and the follow-up visit is 15-min.

**Table 2 Tab2:** Intervention and control insoles

Contoured foot orthoses (intervention)	Sham flat insole (control)
Blue Formthotic^TM^ (Foot Science International) Blue, medium density (140 kg/m^3^ single-density, closed-cell polyethylene foam) prefabricated Formthotic^TM^ which possesses heel and arch support. A first MTP joint cut out is added if tolerated, and a blue 4°medium density varus wedge is added if the Foot Posture Index score is >7.	Blue flat insole (Foot Science International) Blue, medium density (140 kg/m^3^ single-density, closed-cell polyethylene foam) 3mm flat insole.

Images taken from Bonanno et al. [28]

The intervention group receives foot orthoses, protocolised as outlined below to ensure consistency (whilst allowing some individual variation) based on findings from our international survey [20], and developed by expert consensus during our prior feasibility RCT [10]. Specifically, a blue (medium-density) Formthotic™ prefabricated foot orthotic (Foot Science International, Christchurch, New Zealand) is prescribed, and modified using a first MTP joint cut out for joint rotation. If the participant does not have any available first MTP joint range of motion (i.e. joint fusion), or if the cut out elicits immediate pain on walking, then a first ray extension is used instead. Podiatrists score the foot posture index (FPI; a reliable and valid measure of foot posture – see below [29]) and participants with an FPI score > 7 also have a full length 4° varus wedge (Formthotics, Foot Science International, Christchurch, New Zealand) adhered to the plantar surface of the orthoses. Participants in the control group are provided with a sham flat 3 mm prefabricated insole that is the same colour and density and with the same branding as the contoured foot orthoses, but without any heel or arch support. Orthoses/insoles are trimmed (if needed) and fitted into participant’s footwear at the initial visit. If appropriate, the podiatrist will provide advice regarding use of footwear with a wide, deep toe box that is able to accommodate orthoses. If the participant did not bring appropriate footwear that can accommodate the orthoses, they will be encouraged to bring an appropriate pair to the next consultation. At this time, participants are advised to initially commence wearing the orthoses/insoles for 1 h on the first day and to increase use by an additional hour each day, until they are wearing them at all times when shod for 12 weeks. The orthoses/insoles are reviewed at the follow up visit, and additional modifications to address comfort or adverse events (such as trimming the length) may be provided (and documented), if necessary.

Eight podiatrists (three in Melbourne, three in Sydney, one in Brisbane and one in the Gold Coast) were recruited from our clinical networks. The study podiatrists have a minimum of 2 years’ experience treating people with first MTP joint OA. Podiatrists were sent a study manual and completed a one-hour online training session where they were trained in study protocols. Podiatrists were also sent treatment notes which outline each step of the intervention, and which they are required to complete for each participant, to ensure trial fidelity.

## Outcome measures

### Primary outcome

#### First MTP joint pain on walking

Overall average pain intensity on walking in the last week is assessed at baseline and 12-weeks using an 11-point numerical rating scale (NRS) with terminal descriptors of ‘no pain’ (score = 0) and ‘worst pain possible’ (score = 10). This was chosen because it has well established clinometric properties in OA [30] and is a recommended outcome measure for OA RCTs [31].

### Secondary outcomes

#### Foot pain

Foot pain over the past week is measured using the pain subscale of the Foot Health Status Questionnaire (FHSQ), a foot-specific tool with high internal consistency and test-retest reliability [32]. This subscale contains 4 questions related to overall foot pain, each rated on a 5-point Likert scale from 0 (none) to 4 (severe). Responses are recoded to provide a score between 0 (worst foot health) to 100 (optimal foot health).

#### Physical function

The function subscale of the FHSQ is used to assess physical function over the previous week [32]. This subscale contains 4 questions related to how much foot pain interferes with specific activities, each rated on a 5-point Likert scale from 0 (not at all) to 4 (extremely). Responses are recoded to provide a score between 0 (worst foot function) to 100 (best foot function).

#### Overall first MTP joint pain

Overall average pain intensity in the last week is scored on an 11-point NRS, with terminal descriptors ‘no pain’ (score = 0) and ‘worst pain possible’ (score = 10).

#### Participant-perceived change

Participants rate their change in i) pain; ii) function; and iii) overall (from baseline) over the 12 weeks of the study via a 7-point Likert scale (from ‘much worse’ to ‘much better’) [33]. Participants are classified as improved if they report being ‘moderately better’ or ‘much better’.

#### Health-related quality of life

Health-related quality of life is measured using the Assessment of Quality of Life (AQoL-6D) instrument, which has strong psychometric properties and is more responsive than other widely-used scales [34]. The AQoL-6D contains 20 items assessing independent living, mental health, relationships, pain, coping and senses. Scores range from − 0.04 to 1.00, with higher scores indicating better quality of life.

#### Physical activity

Physical activity over the previous week is measured using the Physical Activity Scale for the Elderly (PASE) [35] which has been validated against accelerometry [36]. Scores range from 0 to > 400, where higher scores indicate more physical activity.

### Other measures

#### Co-interventions

Participants self-report visits to health care providers, use of prescription and over the counter medication, hospitalisation and/or investigative procedures over the previous 7 days in monthly log books, and over the previous 12 weeks via a custom survey at baseline and 12 weeks.

#### Adverse events

Adverse events, defined as any problem experienced in the study first MTP joint or other body region due to wearing the study insole, are recorded by podiatrists in treatment notes, self-reported in log-books and ascertained by open-ended questioning via a custom survey at 12 weeks. The proportion of participants experiencing adverse events, and the nature of the adverse events, will be described.

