### Sample size calculations

The minimal clinically important difference (MCID) in our primary outcome is a change in NRS walking pain of 1.8 out of 10 units [39]. We assume a between-participant standard deviation of 2.5 and a baseline to 12-week correlation of 0.3 using our pilot RCT data. Using ANCOVA adjusted for baseline score, we need 37 participants per arm to achieve 90% power to detect the MCID in pain. Therefore, we will recruit 44 people per arm in total (*n* = 88) to allow for 15% attrition. We have not adjusted the sample size for clustering because podiatrists treat a similar proportion of participants from each group.

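### Adverse events count only when attributed to the insole, and one of the three recording sources is the unblinded podiatrist

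*Protocol article*

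**What the plan says.** Under Adverse events, the protocol article gives the definition and the first source together: "any problem experienced in the study first MTP joint or other body region due to wearing the study insole, are recorded by podiatrists". In full, events "are recorded by podiatrists in treatment notes, self-reported in log-books and ascertained by open-ended questioning via a custom survey at 12 weeks". The analysis is descriptive: "The proportion of participants experiencing adverse events, and the nature of the adverse events, will be described".

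On blinding, the section on randomisation, blinding and allocation concealment says "The podiatrists administering the insoles will not be blinded", while for participants "Limited disclosure is used to blind participants to group allocation". On contact, Insole interventions says "Participants in both groups have two visits with a study podiatrist, one in week 1 and one in week 3". The same section makes the second visit the point at which the insole is reviewed and any changes made for comfort or adverse events are documented.

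The article states no blinded or independent attribution step and no count of problems irrespective of cause.

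**The concern.** Attribution is part of the definition, so it acts as an entry condition. A problem that nobody links to the insole is not an adverse event under this rule, and no later analysis can restore a record that was never made.

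A sham control offers something better. If every problem is counted in the same way in both arms, the randomised comparison itself shows whether the device causes harm, and nobody has to decide case by case. That matters here because foot and joint complaints are hard to attribute individually in people with osteoarthritis.

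One of the three sources is also completed by someone who can see which device was supplied. The contoured orthosis has heel and arch support, usually a cut-out and sometimes a wedge; the sham is a flat 3 mm insole. If podiatrists attribute complaints more readily to one device than to the other, the recorded proportions can differ when the true ones do not, or agree when the true ones differ. What is at stake is the trial's safety result. The primary outcome is not affected.

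**Working it through.** **1. The plan's own figures.** The article gives no adverse event rate, so there is none to reproduce. The only figure borrowed below is 44 per arm. It reproduces: 2 × 2.5² × (1 − 0.3²) × (1.960 + 1.282)² / 1.8² = 36.9, so 37 per arm (two-sided 5% level assumed, as none is stated), and 37 / 0.85 = 43.5, so 44.

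**2. Who attributes, and with what knowledge.**
- Podiatrist treatment notes: unblinded; visits in weeks 1 and 3.
- Participant log-books: blinded by limited disclosure.
- Participant survey at 12 weeks, open-ended: blinded by limited disclosure.

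The article says podiatrists record events; it does not say they judge them. Recording under a definition that requires causation nevertheless needs an attribution.

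**3. A model for the size.** All inputs here are assumptions:
- p, the true proportion with a problem, equal in both arms: 0.20 or 0.40
- a, the chance that a blinded participant attributes the problem to the insole, equal in both arms: 0.3, 0.6 or 0.9
- b, the chance that the podiatrist's notes attribute it to the insole, orthoses v sham: 0.4 v 0.1, 0.6 v 0.2, or equal at 0.5
- the two channels act independently, and an event counts if either reports it

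Recorded rate = p × [1 − (1 − a)(1 − b)].

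Spurious gap, combined sources = p × (1 − a) × (b_orthoses − b_sham).

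Spurious gap, podiatrist notes alone = p × (b_orthoses − b_sham).

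**4. Results.**
- Combined, smallest: 0.20 × 0.1 × 0.3 = 0.006, or 0.6 points (18.8% v 18.2%).
- Combined, largest: 0.40 × 0.7 × 0.4 = 0.112, or 11.2 points (28.8% v 17.6%).
- Podiatrist notes alone: 0.20 × 0.3 = 0.06 to 0.40 × 0.4 = 0.16, or 6 to 16 points.
- Equal podiatrist attribution: the gap is 0 throughout.
- If podiatrists attribute more readily to the sham, the signs reverse.

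**5. Loss without any bias.** With b = 0.5 in both arms, a true 20% is recorded as 13%, 16% or 19% for a = 0.3, 0.6 or 0.9, and a true 40% as 26%, 32% or 38%. The definition drops problems even when the arms are treated alike.

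**6. Sensitivity to independence.** If podiatrists note only problems that the participant also attributes to the insole, the notes add nothing and the combined gap is zero. If they mostly note problems the participant does not attribute, the gap moves towards the podiatrist-only figure.

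**The case against.** A reader might infer that the whole safety comparison passes through the podiatrist. Suppose 30% of each arm has a problem, with attribution of 80% v 40%. Then 0.30 × 0.80 = 24% and 0.30 × 0.40 = 12%, a 12-point excess, or about 11 v 5 of 44 participants. The article does not support that reading, because two of the three sources are blinded participants. Keep those rates and let participants attribute 60% in both arms: 0.30 × (1 − 0.4 × 0.2) = 27.6% against 0.30 × (1 − 0.4 × 0.6) = 22.8%, a gap of 4.8 points. If the podiatrist sees only a quarter of the problems, which is plausible with two early visits, b becomes 0.2 v 0.1. The rates are then 20.4% v 19.2%, a gap of 1.2 points or about half a participant of 44. This objection stands.

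Nor is it right that unattributed problems leave no trace. Co-interventions collects care visits, medicines, hospital stays and investigations. The section on pain at other sites collects the number and severity of painful areas. Treatment adherence collects why and when insoles were abandoned. None of these carries a causal filter. This also stands in part. What remains uncovered is a non-pain problem that led to no care, medication or stopping, and these items do not make an all-cause adverse event count.

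Nothing in the article shows that podiatrists would over-attribute to the contoured device. The forms are not shown either, so whether all three carry the causal wording is unknown.

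Finally, adverse events are only described, with no planned test. That limits the weight of the point but does not remove it, because described proportions will still be read by arm as the trial's safety result.

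**Conclusion.** The point holds in a limited form. The definition excludes problems not attributed to the insole, and one of three sources applies it with knowledge of allocation. The described proportions are therefore incomplete and may be distorted through that one channel.

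The ranges in the working (0.6 to 11 points combined, 6 to 16 in podiatrist notes alone, zero under equal attribution) illustrate what is possible and are not estimates. They rest on assumed problem and attribution rates and on independent channels, and the article fixes neither sign nor size. The change is worth making, because the lost records cannot be recovered at analysis and the suspension of recruitment gives an opportunity to make it.

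**What to change.** Before recruitment restarts:
- Define an adverse event as any new or worsened problem since receiving the insole, whatever the suspected cause.
- Reword the treatment notes, log-books and 12-week survey wherever they carry the causal wording.
- Record suspected relatedness as a separate field.
- Describe all-cause and related proportions by arm and by source, podiatrist against blinded participant, so that any effect of the unblinded channel is visible.

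**Cost.** At most three existing forms need rewording; the primary outcome, sample size and interventions are untouched. More minor, unrelated events will be recorded. Participants already followed came under the narrower definition, so results must be reported by form version. Timelines puts recruitment from August 2019 to the March 2020 suspension, about seven of the nine months planned to May 2020. The article does not say how many had been enrolled, so one or both versions may hold small counts among the 88.
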